## Abstract

**Background:**

Obesity is not only a highly prevalent disease but also poses a considerable burden on children and their families. Evidence is increasing that a lack of self-regulation skills may play a role in the etiology and maintenance of obesity. Our goal with this currently ongoing trial is to examine whether training that focuses on the enhancement of self-regulation skills may increase the sustainability of a complex lifestyle intervention.

**Methods/Design:**

In a multicenter, prospective, parallel group, randomized controlled superiority trial, 226 obese children and adolescents aged 8 to 16 years will be allocated either to a newly developed computer-training program to improve their self-regulation abilities or to a placebo control group. Randomization occurs centrally and blockwise at a 1:1 allocation ratio for each center. This study is performed in pediatric inpatient rehabilitation facilities specialized in the treatment of obesity. Observer-blind assessments of outcome variables take place at four times: at the beginning of the rehabilitation (pre), at the end of the training in the rehabilitation (post), and 6 and 12 months post-rehabilitation intervention. The primary outcome is the course of BMI-SDS over 1 year after the end of the inpatient rehabilitation. Secondary endpoints are the self-regulation skills. In addition, health-related quality of life, and snack intake will be analyzed.

**Discussion:**

The computer-based training programs might be a feasible and attractive tool to increase the sustainability of the weight loss reached during inpatient rehabilitation.

**Trial registration:**

The present study protocol was registered on 13 July 2015 at German Clinical Trials Register: DRKS00007879.

## Background

Obesity remains the most serious health threat worldwide. To take the example of Germany, approximately 6.1 % of the children and adolescents are obese [1]. Childhood obesity is already associated with various adverse outcomes such as hypertension, dyslipidemia, hyperinsulinemia and prediabetic state. In addition, obese children and adolescents exhibit reduced psychosocial functioning, especially those seeking treatment [2, 3]. Obesity is not only highly prevalent in childhood, but substantial forward tracking of obesity into adulthood also exists [2]. The economic burden of obesity and its related comorbidities is enormous. Thus, obesity is associated with 0.7 to 2.8 % of health-related expenditure linked to society; obese individuals cause 30 % more direct costs compared to normal-weight individuals [4]. In addition, an increased rate of sick days [5] and reduced opportunities for higher education and on the labor market [6–8] are reported.

Today’s living conditions and food habits in children and adolescents are generally characterized by a combination of increased energy consumption and sedentary lifestyles, which strongly favor the emergence of overweight and obesity. In this obesogenic environment, children and adolescents are particularly challenged to develop and maintain a high “resistance” against the ready availability of food.

Therefore, self-regulatory skills are considered to be a relevant factor in the formation and maintenance of obesity. Self-regulation refers to automatic and conscious processes that enable individuals to control their thoughts, impulses, emotions, and attention, as well as their performances [9]. It includes, among other things, the ability to postpone rewards, to pursue long-term goals or suppress impulses (so-called inhibitory control). Obese children exhibit deficits in various aspects of self-regulation compared to normal-weight children (see also reviews by [10–13]). It is challenging for overweight children to stop an activity that is already mentally planned (for example, [14, 15]) or to postpone rewards, especially when it comes to food-related stimuli (for example, [16, 17]). A low amount of self-regulatory skills has been proven as a predictor of weight increase in prospective studies. Pauli-Pott, Albayrak, Hebebrand, and Pott [18] could show that a lack of inhibitory control will negatively impact a healthy weight development especially in younger children (age 8). In addition, Tsukayama, Toomey, Faith, and Duckworth [19] suggest in their longitudinal study that children who have a high impulse control and enhanced ability to delay gratification at the age of 9 years are significantly less likely to be overweight at the age of 15 compared to their less controlled peers. They conclude that the ability to self-regulate and control enables individuals to maintain a healthy weight status. Similar findings have been reported by Seeyave et al. [20].

The ability to maintain the weight at a healthy weight range in the long term is the ultimate goal of intervention programs. Overall, the empirical data on the effectiveness of treatment programs in childhood and adolescence is cautiously optimistic: meta-analyses [21–24] have suggested that, in most cases, a small but clinically meaningful weight loss can be achieved. However, many studies only included short-term follow-up periods, and the long-term maintenance of weight changes presents the major challenge. Even in the area of medical inpatient rehabilitation, an important healthcare forum for the treatment of obese children and adolescents in Germany (30 % of obese children are treated in these settings [25]), recent data indicate that approximately 20 % of children and adolescents had already exceeded their relative standardized BMI-score (BMI-SDS) 1 year after the end of rehabilitation compared to its beginning (Warschburger P, Kröller K, Haerting J, Unverzagt S, Egmond-Frohlich A van: Empowering parents of obese children (EPOC): A randomized-controlled trial on additional long-term weight effects of a parent training, submitted). Strategies to ensure weight-loss maintenance are therefore urgently needed. A computer-based self-regulation training could represent a promising approach. In the field of research on alcoholism, positive effects of such an additional training program have been reported. Alcoholic and nonalcoholic pictures are presented on the computer screen and the task is to either to pull or push the joystick in order to enlarge or decrease the size of the picture. Wiers, Eberl, Rinck, Becker, and Lindenmeyer [26] trained the rejection (avoidance) of alcoholic beverages in combination with an approach response of nonalcoholic beverages during four computer sessions of 15 min each. The authors could show that the rejection of alcoholic beverages can be learned and that positive implicit attitudes toward alcohol decreased after the training. Data from the 1-year follow-up underscore the clinical relevance of the training: a significantly lower relapse rate in the training compared to the control group was observed.

Taken together, research findings suggest a lower expression of self-control skills and greater attention on food-related stimuli for overweight children. Evidence suggests that self-control and performance skills can be used successfully for training during childhood and adolescence [27]. Henceforth, based on the promising results of an approach-avoidance training for adults, self-regulation training will be adapted for overweight children and adolescents in order to train their avoidance skills when confronted with high-caloric food stimuli. Evaluation of short- and long-term effects of the training on behavioral tendencies and weight development will be studied in a multicenter, placebo-controlled study. Given the common cognitive and neural mechanisms of alcohol and “overeating” [28], it is assumed that a nutrition-specific version of the “Approach-Avoidance Training” (AAT) can also be successfully applied in the context of obesity treatment.

## Methods/Design

### Study design

The Self-Regulation Training Joystick (SRT-Joy) is a multicenter, prospective, parallel group, randomized-controlled superiority trial for the evaluation of the efficacy of a computer-assisted individual self-regulation training compared to a placebo control group. Depending on their intervention allocation, children play either the SRT-Joy computer task or the placebo training. In order to obtain information on the transfer of increased self-regulation skills to everyday life, two follow-up measurements after the end of the inpatient rehabilitation stay will be realized. Hence, the four time points for measurement are given below: start of the child’s inpatient stay and beginning of the computer training (T1), end of the child’s computer training during the inpatient stay (T2), 6 months after the child’s inpatient stay (T3), and 12 months after the child’s inpatient stay (T4). The trial flow is depicted in Fig. 1.

**Fig. 1 Fig1:**
[figure not shown]
Trial flow chart

### Study setting

This study is being conducted in four study centers, all of which are inpatient medical rehabilitation facilities (Bad Kreuznach, Bad Orb, Idar Oberstein, and Sylt). These clinics were chosen because of their specialization in the treatment of childhood obesity and delivering their intervention according to the national guidelines. Participating study centers and investigators are fully listed in the German Clinical Trials Register (DRKS00007879).

### Recruitment

After initiation of the study centers, the 12-month recruitment phase of this ongoing trial started in March 2015. Eligible subjects will be recruited consecutively at their arrival at the clinic. A study coworker will inform the parents and their children about the contents and aims of the study and ask for written informed consent. Participation is voluntary and parents and children can withdraw informed consent at any time without any disadvantages for their treatment within the inpatient treatment facility.

### Participants

In order to ensure a high representativeness of our study results, only a few inclusion and exclusion criteria were defined as listed below:

#### Inclusion criteria

Inclusion criteria are as follows:aged 8 to 16 years at recruitment,obesity as defined by body mass index (BMI) exceeding the 97th percentile [29] based on a medical examination on arrival in the clinic, andinformed consent to participate in the study from both the parents and their child.

#### Exclusion criteria

Exclusion criteria include the following:secondary obesity as a consequence of other diseases (such as endocrine or genetic diseases; determined by medical examination),mental retardation,physician-ordered pharmacological therapy for attention-deficit-hyperactivity disorder, orobligatory treatment plans that interfere with the participation in the computer training.

Prior to study inclusion, children will undergo a thorough medical examination.

### Sample size and enrolment

So far, there are no studies that have conducted an AAT on nutrition in children. Therefore, a referral upon existing data could not be used in the power calculation. In total, we only expect small differences between the groups for the primary outcome (age- and gender-specific BMI-SDS course after 6 to 12 months following the intervention), because the AAT will only be an additional offer for children and adolescents within the multidisciplinary rehabilitation. Comparable effect sizes are also assumed for food intake and weight-related quality of life. On the other hand, we expect average effect sizes for the employed self-control measures as secondary outcomes because the AAT is a specific training of these skills. The power calculation was performed with the program *g power 3.1* [30] in several steps to take into account these considerations. The power was set to .8 and the alpha error to .05. For a small effect (f = .2), 199 subjects are needed, with 99/ 100 per group for an analysis of covariance (ANCOVA) that includes three covariates (age, gender, and educational background). Because the data will be primarily analyzed on the basis of an intention-to-treat approach, only a small number out of the 13 patients per group were taken into consideration (see [22]). A subsequent post-hoc compromise analysis (considering differing effect sizes for primary and secondary outcomes) has confirmed that this sample size (n = 226) is sufficient to depict small effects with a power of .9. On that basis the following will occur:n > 600 will be assessed for eligibility,n = 226 will be allocated to trial, andan intention-to-treat approach (ITT) will be conducted on n = 226 (the complete analysis should include n = 199 participants).

To prevent selective drop out and incomplete outcome data, all participants will be reimbursed for completely filling in the questionnaires in the follow-up period and will receive cheerful mail on special occasions (birthday, Easter or Christmas greetings). In addition, the family doctors will receive a monetary incentive for providing anthropometric data (weight and height).

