### Randomization procedure and treatment allocation

Randomization and allocation in a ratio of 1:1 for each clinic to treatment aim will occur before the interventions begin. The randomization is computer based [40] and centrally performed. A post-hoc evaluation by descriptive statistical comparisons between the intervention and the control group in relevant sociodemographic data (age, gender, and sociodemographic data) will be conducted to assess the effectiveness of the randomized assignment. The study assistant will receive the fax with the randomization that only discloses the allocation of the patients to either group A or B (allocation concealment).

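### The power of .9 stated for n = 226 does not hold at the plan's alpha of .05: with f = .2 it is .85 if all 226 are observed and .80 on the expected 199

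*Protocol article*

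**What the plan says.** All of the power statements stand in the protocol article under Sample size and enrolment. The operating characteristics are given once: "The power was set to .8 and the alpha error to .05". The primary calculation follows: "For a small effect (f = .2), 199 subjects are needed", for an "analysis of covariance (ANCOVA) that includes three covariates (age, gender, and educational background"). An allowance of 13 children per group brings the total to 226. The planned analysis sets are described as "intention-to-treat approach (ITT) will be conducted on n = 226 (the complete analysis should include n = 199 participants").

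A second power step, labelled a post-hoc compromise analysis that took account of different effect sizes for primary and secondary outcomes, then "has confirmed that this sample size (n = 226) is sufficient to depict small effects with a power of .9". No alpha, beta/alpha ratio or numerical effect size is given for this step. No alpha other than .05 appears anywhere in the article.

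**The concern.** A reader meets three statements in one paragraph: alpha is .05, small means f = .2, and 226 children give power .9 for small effects. The natural reading joins them, and joined they do not agree with the calculation that produced 199.

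The label of the second step points to the reason. A compromise power analysis does not hold alpha fixed. It fixes the ratio of beta to alpha and solves for both, so alpha is an output. A power obtained that way describes a test at the solved alpha, not at .05.

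What is at stake is how a null result will be read. The same section expects only small group differences on BMI-SDS. On the printed figure, a non-significant primary result would be taken as having had a 10% chance of missing f = .2. On the plan's own stated terms, that chance is 15% to 20%.

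**Working it through.** **Inputs, from the protocol article**
- Two arms, 1:1 ("Randomization and allocation in a ratio of 1:1 for each clinic"); numerator df = 1.
- Three covariates: age, gender, educational background. Denominator df = N − 2 − 3 = N − 5.
- f = .2. For two equal arms d = 2f = .4.
- Alpha .05. Sidedness is not stated, but the ANCOVA F-test is non-directional.
- N = 226 allocated, 199 expected in the complete analysis.

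**Formula.** Power = P(F′ > Fcrit), where F′ is noncentral F with (1, N − 5) df and λ = f² × N, and Fcrit is the 95th percentile of the central F.

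**Step 1: reproduce the plan's 199**
- N = 198: λ = .04 × 198 = 7.92, power .7996.
- N = 199: λ = .04 × 199 = 7.96, power .8016.

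The smallest N reaching .80 is 199, as stated. A one-sided .05 test would need only about 156 for power .8, so the stated 199 fixes the two-sided reading.

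**Step 2: the same model at 226**
- λ = .04 × 226 = 9.04, df = (1, 221), power .849.

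That is about 5 points below .9.

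**Step 3: what power .9 would need**

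| Held fixed | Solved for | Result |
|---|---|---|
| f = .2, alpha .05 | N analysed | 265 |
| N = 226, alpha .05 | f | .217 |
| N = 226, f = .2 | alpha | .086 |

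The last row does not depend on any beta/alpha ratio.

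**Step 4: where the .9 may come from.** Solve beta = q × alpha at N = 226, f = .2. The ratio q is an assumption, because the article gives none.

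| q | alpha | power |
|---|---|---|
| 1 | .094 | .907 |
| 2 | .064 | .873 |
| 4 | .042 | .832 |

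Of these, q = 1 matches the printed figure.

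**Step 5: the expected complete cases.** 226 − 199 = 27 children are not expected in the complete analysis. Data analyses says missing primary outcomes will be filled by the EM algorithm. Imputed values add no observed outcome information, so 226 is the best case and 199 the planned case: .849 against .802.

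**Step 6: sensitivity to baseline adjustment.** Data analyses adjusts the ANCOVA for baseline, which is not among the three covariates in the calculation. If f = .2 is on the scale before that adjustment, the effective value is f / √(1 − r²), with four covariates. The correlation r is not in the article, so these values are assumed.

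| r | effective f | power, N = 226 | power, N = 199 |
|---|---|---|---|
| .4 | .218 | .904 | .865 |
| .5 | .231 | .933 | .900 |
| .8 | .333 | above .99 | above .99 |

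**The case against.** The strongest reply is that the sentence never attaches .05 to the .9. It names a different method, in which alpha is solved for, and with a ratio of 1 that method returns .907. On this view nothing is miscalculated, and the fault is only an undisclosed ratio and alpha. This stands as an explanation of the figure. It does not rescue it: no ratio gives .9 at f = .2 and n = 226 without an alpha of about .086 or more, and the article sets no such alpha for any test. The ratio of 1 remains an inference.

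A second reply is that baseline adjustment could lift true power to .9 at alpha .05. That is possible, as Step 6 shows, but the article states no baseline correlation and its calculation lists only the three demographic covariates. The printed .9 therefore cannot be credited to it. The point does limit what may be said against the trial: .80 to .85 holds only if f = .2 is net of baseline as well.

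A third reply is that the mention of differing effect sizes covers the figure. At f = .25 power would be .96 at 226, but the sentence claims .9 for small effects, and this section puts small at f = .2.

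A reader might also infer that the trial has only about 30% power for a small effect and is not powered for anything below f = .2. The documents do not support that as an error. They define small as f = .2; calling f = .1 small is an outside convention. At f = .1, net of covariates, power is .29 (N = 199) to .32 (N = 226), which is context only. On the scale before baseline adjustment, it would be .37 at an assumed r = .4 and .70 at r = .8 (N = 226).

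**Conclusion.** The concern holds in a limited form. The 199 is correct. The power of .9 at n = 226 is not a correct statement for f = .2 at the only alpha the plan sets: the value is .85 with no missing outcomes and .80 on the expected complete cases, a shortfall of 5 to 10 points. This rests on the plan's own model (two-sided F-test, three covariates, f already net of every covariate in the ANCOVA).

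The discrepancy is probably not an arithmetic slip but a compromise result reported without its alpha; that explanation depends on the assumed ratio of 1, while the shortfall does not. It would go too far to say that the trial cannot reach .9 or cannot detect smaller effects, because the gain from baseline adjustment is unknown.

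**What to change.** Replace the compromise-analysis sentence with:

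> At two-sided alpha = .05 and f = .2 (d = .4, taken as net of all covariates in the ANCOVA), power is .80 with 199 analysed and .85 with 226 and no missing outcomes.

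If the .9 is to stay, print beside it the alpha and the beta/alpha ratio it rests on. If the sponsor wants to claim more power from the baseline adjustment described under Data analyses, state the assumed baseline correlation and the resulting power. Figures for f = .1 may be added as context if they are labelled as net of covariates; any remark on power for smaller effects needs the same qualification.

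The cost is wording only. Enrolment, test and analysis are unchanged, and the stated power becomes less favourable.

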### Intervention and controls

#### Basic interventions for all children

The inpatient stay usually encompasses a period of 4 weeks. During their stay, all children and adolescents will participate in a multidisciplinary lifestyle intervention, which includes cognitive-behavioral group training, nutrition education, and diet modification, as well as activity sessions several times a week. This complex treatment approach focuses on the increase in physical activity, the decrease in sedentary behavior, the change in eating habits, and the relative reduction of weight. The AAT treatment will be implemented as a supplemental treatment offer of the clinics.

#### SRT-Joy Approach-Avoidance-Training: intervention

Children and adolescents far too often eat high-caloric snacks and too seldom vegetables [31]. Therefore, they should learn, in the context of the computer-based training, to push high calorie snacks away and to pull vegetables with the joystick toward themselves. In a pilot study, these foods have been tested on their familiarity and have been matched according to their color. All foods are presented on white either square or round plates. Children are instructed to use the approach response with the round plate (pull) and the avoidance response (push) with the square one using the joystick. Thereby, the vegetables are always located on the round plates and the snacks on the square plates (implicit approach-avoidance training). Contingent with their actions, the photos on the screen get either larger or smaller. A short instruction phase ensures that the children have understood the instructions. This phase is followed by a test trial (pre-test data) and the training phase (including six training blocks). In each training session, the children will view 120 pictures. Compatible (vegetables on round plates, snacks on square plates) and incompatible stimuli are balanced per trial. The training phase is followed by an assessment of the post-data and a booster training. At the end of each training session, the children receive a feedback on their error rate and their reaction time. The training sessions take approximately 15 to 30 min each and are conducted during 3 consecutive days followed by a pause of 4 days over the course of the first 2 weeks of rehabilitation (six appointments).

#### Placebo: control

The children and adolescents of the control group participate in an identical number of training sessions with the same structure as the intervention group. In contrast with the intervention group, children will approach and avoid both (high-calorie snacks and vegetable) at the same rate so that no learning effect occurs.

#### Measures of intervention attendance, treatment integrity and standardization

The intensity of treatment and compliance can be assessed by the PC, as the times and dates of practice are logged, as soon as the children log in with their code (the training times of child are used as a marker of compliance). In addition, the clinics document the other treatment approaches that were carried out. The standardization of the intervention and treatment integrity is given inherently by training on the PC.

